#### Materials and training

The programme will be implemented in five day-activity centres, the other five day-activity centres participate as control group. Together with the movement experts, a list of basic low-cost materials to perform the physical activities is drafted and purchased, including heart rate monitors. We developed a one-day training for physical activity-instructors, with the aim to teach them about the physical activity framework and how to design the physical activity programmes, that address the needs and interests of the target group, and is consistent with the underlying programme theories. They will also learn how to apply the heart rate monitors. The staff of the participating day-activity centres also will receive a one-day training, developed by a professional trainer, about the education programme. They receive information about why physical activity is important for their clients and about the goals and structure of the education programme. In addition, they will practice preparing and conducting the exercises and how to adapt exercises to the needs of their group.

#### Monitoring execution of the programme

A *workgroup* will be formed in each day-activity centre that consists of the programme’s conductors, a physical therapist, a behavioural therapist and the researcher. This working party will meet every five to six weeks to evaluate the execution of the programme and establish solutions for the barriers that will be presented. Four months after the intervention has started, two evaluation meetings will be held to discuss barriers they met and exchange successful strategies for optimal participation of the seniors. One concerning the education programme with all staff members of the five participating day-activity centres and one with all the movement experts, involved with executing the physical activity programme.

Step 6: Evaluation

The evaluation includes an effect evaluation and a process evaluation. The main outcome variable in the effect evaluation is physical activity level, and will be measured with a pedometer that will be worn for at least 4 days [32]. The NL-1000 (New-Lifestyles, Missouri USA) is a hip-worn device that measures vertical acceleration, using a piezo-electric accelerometer mechanism. It measures reliably at a walking speed of 3.2 km/h or higher [33,34]. Secondary outcome measurements include: muscle strength, balance, walking speed, blood pressure, aerobic capacity, weight, waist circumference, serum glucose, serum cholesterol, mobility, daily living skills, depressive symptoms and functional deterioration. Measurement instruments that are selected in the epidemiological study HA-ID and that were proven to be reliable among people with ID [31] are used for data collection.

All outcomes will be measured at baseline and after eight months, at the end of the intervention period. Health outcomes (motor fitness, cardio respiratory fitness and morphological fitness) will be assessed in or near the day-activity centers and performed by specially trained physical therapists and medical assistants, experienced in supporting seniors with ID [31]. Caregivers working at the homes of the participants and behavioral therapists will receive several checklists and/or questionnaires by mail (about mobility, daily living skills, depressive symptoms and functional deterioration).

The process evaluation will entail analysis of data on the attendance, barriers, initial use, exposure and continued use after the intervention period. Physical activity-instructors will fill in registration forms during the intervention period about e.g. attendance and participation of each senior and the content and duration of each physical activity. Participants, programme leaders, and managers will be interviewed and/or receive a written questionnaire about barriers and continued use of the programme at the end of the intervention period.

#### Analysis

Generalized estimation equations will be used to identify significant differences in the primary and secondary outcome measures between participants and controls, correcting for day-activity centre as cluster. The outcomes at the end of the intervention for the control group and participation group will be compared, adjusted for outcome differences at baseline.

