#### Selection of day-activity centres and participants

This study is conducted by a Dutch consortium of three large ID care provider services and the Intellectual Disability Medicine research group of the Erasmus Medical Centre at Rotterdam, in collaboration with the Centre of Human Movement Sciences of the University Medical Centre Groningen. HA-PAP is set in the three large ID care provider services, that include nineteen day-activity centres offering recreational activities to the target group. Two day-activity centres with reorganization problems or substantial personnel problems are excluded. Based on earlier research, we expect to obtain informed consent for about 50% of the participants [31]. Because we planned to conduct the intervention in groups of eight to ten seniors (see Paragraph: development of the programme), 7 day-activity centres with less than 15 seniors with mild or moderate ID are excluded. The ten remaining centres all have a large activity-room or a gymnasium facility in-house or nearby.

Our primary outcome measure is physical activity, defined as steps per day. We have data of seniors with a mild or moderate ID from the pilot of the study: “Healthy Ageing with Intellectual Disabilities” (HA-ID) [31] at our disposal (n = 37), in which we found a mean physical activity level of 5480 steps per day (SD 2146). With a power of 80% to detect a difference of 1073 steps (effect size 0.5) and a type I error of 0.10, 60 seniors in both the control group and the participation group are required. We assume a drop out of 20% and planned to start therefore with 80 seniors in each group.

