#### Randomization

To help ensure comparability of the participants conducting the programme and the seniors in the control group, we looked for the best possible match with respect to sex, age, intellectual disability, the use of a walking aid and provider service. The matching procedure was conducted with the data of the potential 237 participants (see previous Paragraph) using chi-square and t-tests. The best match was found when the ten day-activity centers were divided into two specific groups of five centres each. We subsequently checked the comparability of important day-activity centres’ characteristics in both groups, that is the availability of a gymnasium nearby and involvement of a physical-activity instructor in the day-activity centres’ activities. These characteristics appeared to be comparable. The chairman of the steering group, in presence of the researcher and a senior staff member Public Relations, randomly selected one of the two groups of five day-activity centers who will conduct the programme. The remaining group of five day-activity centres will serve as the control group. Because the implementation of the programme has to be prepared and organized, the sequence is only concealed for the clients and family, not to the day-activity centres’ managers. After the informed consent procedure has ended, all participants and/or their family will receive a confirmation of participation in the study and information about the intervention allocation.

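### GEE is planned for all outcomes with only ten centres and no small-sample safeguard named; with the usual uncorrected sandwich z-test, the stated 0.10 error rate would become about 17–22%, or roughly 10–19% if matching helps

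*Protocol article*

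**What the plan says.** The Analysis section consists of two sentences. The first fixes the method for every outcome: "Generalized estimation equations will be used to identify significant differences in the primary and secondary outcome measures between participants and controls". All it says on clustering is that this is done "correcting for day-activity centre as cluster". The second says that end-of-intervention outcomes are compared between groups, "adjusted for outcome differences at baseline". The Discussion adds only that clusters and baseline differences will be controlled for.

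The number of clusters is fixed elsewhere. The Randomization section reports that "the ten day-activity centers were divided into two specific groups of five centres each", and Materials and training confirms it: "The programme will be implemented in five day-activity centres, the other five day-activity centres participate as control group".

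The only type I error in the article is in the sample size paragraph (Selection of day-activity centres and participants): "a type I error of 0.10, 60 seniors in both the control group and the participation group are required". A 5% level appears nowhere. That paragraph has no intracluster correlation and no design effect, so the GEE is the only place where the plan deals with clustering.

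**The concern.** The sandwich variance of GEE is valid as the number of clusters grows, and ten is few. It is built from squared residuals around fitted values that have been pulled towards the data, so with few clusters it is too small on average. A z-test then also ignores how imprecisely the variance is estimated. Both errors make p-values too small and confidence intervals too narrow.

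The programme could be declared effective on steps per day, or on secondary outcomes analysed the same way, more often than the stated error rate allows. Because nothing else in the design allows for clustering, the validity of the tests rests on this standard error.

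**Working it through.** **The plan's own figure.** The article gives no error rate for the GEE, so there is none to reproduce. Its nominal level is 0.10, taken from the sample size paragraph.

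**Inputs from the article.** Ten centres, 5 versus 5, hence 10 − 2 = 8 between-centre degrees of freedom. GEE with centre as cluster, adjusted for baseline. Analysed seniors per centre: 60/5 = 12, or 80/5 = 16 with no loss.

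**Assumptions not in the article.** Intracluster correlation 0 to 0.10; baseline to follow-up correlation 0.6; Gaussian outcome; exchangeable working correlation; equal centres of 12 or 16, or unequal centres of 6–21.

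**Step 1: check by hand on centre means.** With five centres in an arm and S the sum of squared deviations of their means:
- unbiased variance of the arm mean: S/(4 × 5) = S/20
- uncorrected sandwich variance: S/(5 × 5) = S/25
- ratio: 20/25 = 4/5, so the standard error is √0.8 = 0.894 of what it should be.

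The true two-sided error rate of the z-test is 2·P(t₈ > z·√0.8):
- nominal 0.10: 1.645 × 0.894 = 1.471, giving 17.9%
- nominal 0.05: 1.960 × 0.894 = 1.753, giving 11.8%

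This needs no value for the intracluster correlation.

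**Step 2: simulation under no effect, matching ignored.** 8000 runs per scenario, baseline-adjusted exchangeable GEE, uncorrected sandwich, z-test:

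| Centres | At nominal 0.10 | At nominal 0.05 |
|---|---|---|
| Equal, 12 or 16 | 17–19% | 11–13% |
| Unequal, 6–21 | 20–22% | 14–16% |

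The mean standard error is 81–89% of the true standard deviation of the estimate. A cross-check with a standard GEE routine (1500 runs, correlation 0.05, 12 per centre) gives 18.6% and 11.7%. The result depends on inequality of centre sizes and hardly on the intracluster correlation.

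Other simple choices do not repair it. The model-based standard error with a z-test gives about 17–20% at nominal 0.10. The uncorrected sandwich with t on 8 df gives about 13–17%.

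**Step 3: allow for the matched allocation.** The two sets of five centres were chosen as the best match on sex, age, level of disability, walking aid and provider service. If these factors predict steps, the true variance of the contrast is smaller than in step 2, which partly offsets the bias. Assuming that they explain half of the between-centre variance, two sets of runs give about 12–19% and 10–18% at nominal 0.10, so roughly 10–19%. The offset is small at a correlation of 0.01 and large at 0.10.

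**Step 4: the remedies, on the same centre-means argument.**
- Kauermann-Carroll multiplies the sandwich by 5/4, so the variance ratio is 4/5 × 5/4 = 1, and t on 8 df is exact: 10%. In GEE simulations with unequal as well as equal centres it gave 4–8% at nominal 5%.
- Mancl-DeRouen multiplies by (5/4)², so the ratio is 4/5 × 25/16 = 1.25. With t on 8 df: 1.860 × √1.25 = 2.079, giving 7.1% at nominal 0.10. Simulation gives 6.5–8.0% in one set of runs and about 7–9% in another, falling to 3–6% under the matching assumption.
- A t-test on baseline-adjusted centre means (8 df) gave 4–5% at nominal 5%.

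**The case against.** The strongest reply is that the article does not say what is being criticised. A reader might infer that it plans GEE without any small-sample correction. It does not say so: it names no variance estimator, working correlation or reference distribution, and GEE with a corrected variance is still GEE. The article condenses a fuller protocol, and an analysis plan that is not shown may settle the matter. This stands, and it makes the inflation conditional on the default being used. It does not remove the point. The article commits to both the method and a number of clusters at which the default form of that method fails, and gives no safeguard.

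A reader might also infer false-positive rates of two to three times a nominal 5%. The arithmetic supports about that multiple at 5% (11–16%), but the article never states 5%. At its own 0.10 the multiple is about 1.7 to 2.2 with matching ignored.

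The matched allocation is a fair objection to the size. It can reduce the inflation, and at the lower end of the range nearly remove it. How far it does so depends on how well the matching factors predict steps, which the article does not report.

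Finally, a reader might infer that every p-value and interval would be too optimistic. The simulations used Gaussian outcomes only, and the article does not give the distributions of the secondary outcomes. The direction of the bias is expected to carry over, but its size for those outcomes has not been shown.

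**Conclusion.** The point holds in conditional form. If the uncorrected sandwich variance with a z-test is used on five against five centres, the true false-positive rate at the stated 0.10 is about 17–22% when matching is ignored, and 11–16% if tests are run at 5%. If matching removes about half of the between-centre variance, the rate at 0.10 is roughly 10–19%.

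The direction of the bias without matching follows from the number of centres alone. The exact size rests on assumed centre sizes, a baseline correlation of 0.6, Gaussian outcomes and the unknown benefit of matching. The documents do not support saying that the trial will use the uncorrected test, nor that 5% is its level. The choice should be settled before the outcome data are analysed.

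**What to change.** Keep the GEE estimate, and add one or two sentences naming, for the primary and all secondary outcomes, one of these in advance:

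- a small-sample bias-corrected sandwich variance (Kauermann-Carroll or Mancl-DeRouen) with a t reference on about 8 degrees of freedom, for tests and confidence intervals; or
- a t-test on the ten baseline-adjusted centre means, with 8 degrees of freedom.

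State the significance level and whether tests are two-sided in the same place. If the full protocol or analysis plan already specifies such a correction, it is enough to confirm this.

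The options are not interchangeable. Kauermann-Carroll can stay slightly above the nominal level when centres are unequal. Mancl-DeRouen with t on 8 df is somewhat conservative, and more so under the matched allocation. The centre-means test is the simplest and held its level in simulation without matching. No design change is needed, but all the options widen intervals and lose some power compared with the uncorrected test.

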## Discussion

The development of a day-activity programme to increase physical activity among seniors with mild or moderate ID by following the six steps of Intervention Mapping has resulted in a novel, theory-driven intervention based on strategies proven to be effective in other populations. The programme will be evaluated using a cluster-randomized trial. Analyses will control for clusters and differences at baseline. The programme’s five most important characteristics are 1) Structured multi-component physical activity programme based on the evidence-based guidelines, 2) Embedded in a routine day-activity programme, 3) Executed in peer groups, 4) Conducted by specifically trained movement experts and staff, 5) Supported by an education programme. Next to education, several behavioural change techniques are used to achieve the desired results, including: “Set graded tasks”, “Provide instruction and model/demonstrate behaviour”, Provide feedback on performance”, “Mirroring” and “Prompt rewards contingent on effort or progress towards behaviour and on successful behaviour”. The design of the programme is such that its contents can be tailored to the individual participant. An effect and process evaluation is being performed in a randomized clinical trial design.

Seniors with ID, experts in working with seniors with ID and managers involved with the implementation of the intervention, have had an important influence on the main concepts of the underlying programme. The experts who will conduct the programme played a central role in putting together a suitable programme and will offer the exercises using methods and strategies that fit best to the capacities, skills and needs of the participants with ID. By organising the intervention in the day-activity setting, there are no extra costs for the participants, the activities are nearby, and staff is available to support them in performing the activities. Although more health or fitness effects might be attained by individual fitness programmes with specific equipment, such a high-cost programme has no chance of being implemented on the long run. By selecting group activities and low-cost materials, we increased the feasibility and the likelihood of the programme’s future implementation. Also the fact that the developed programme allows the programme leaders to tailor the programme to the abilities and interests of the target group, permits a broad implementation.

We found that Intervention Mapping is a useful tool to develop a theory-based programme, including strategies that appeared effective in other subgroups. To our knowledge, the used physical activity guidelines and behavioural change techniques have never been applied to and evaluated in older persons with ID. Therefore, the programme’s effectiveness still needs to be evaluated. Although health promotion research and practice projects have been expanding over the last few years in the field of people with ID, little research has focused on the development and evaluation of theory-based interventions and explicit behavioural change techniques [35,36]. Using but also reporting the underlying theory and behavior change techniques are valuable, because it contributes to the possibility of replicating effective interventions, synthesizing evidence and understanding causal mechanisms underlying behaviour change [26,37]. Marks et al. (2010) developed a health promotion programme based on Social Cognitive Theory and the Transtheoretical model, targeted to adults with mild intellectual disabilities living in the community with limited support. The activity programme included activities in the gym, which were not applicable to our study group, because of lack of fitness equipment in day-activity centres and because these activities could not be conducted in groups of eight to ten older adults with ID.

In conclusion, the HA-PAP programme, is a day-activity programme consisting of a physical activity programme and an education programme. The effect evaluation of the study will provide insight into the programme’s effects on physical activity and health. The process evaluation will provide more insight into the attitudes, facilitators and barriers to the implementation of the programme. If the intervention proves to be effective, a well-developed theory and evidence-based day-activity programme will become available for the promotion of physical activity among seniors with ID. Although this programme was developed explicitly for seniors with ID, we believe that the main programme elements may also be suitable for other subpopulations with similar characteristics, such as older people living in a residential setting and/or people with low-education levels.

## Abbreviations

ACSM: American college of sports medicine; AHA: American heart association; HRR: Heart rate reserve; ID: Intellectual disabilities; IM: Intervention mapping; HA-ID: Healthy ageing with intellectual disabilities; HA-PAP: Healthy ageing- physical activity programme for seniors with intellectual disabilities; PA: Physical activity.
